### Primary end point

The primary end point in this study is the change between baseline and follow-up LVMI (calculated as the ratio: left ventricular mass (LVM)/ body surface area). Two-dimensional and Doppler echocardiography will be performed to quantify left ventricular function and structure (Phillips Healthcare) [21]. Ventricular remodeling will be assessed by calculating LVMI using Devereux formula. Interventricular septum thickness (IVST), left ventricular end-diastolic dimension (LVEDd), left ventricular posterior wall thickness (LVPWT) will be measured by echocardiography. LVM = 1.04[(IVST + LVEDd + LVPWT)^3^-LVEDd^3^]-13.6 g.

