### Statistical considerations

#### Sample size

According to previous study [20], we hypothesized trimetazidine group has an effective rate of 70% to improve the left ventricular remodeling by reducing LVMI and placebo group has 40%, thus 56 patients in each group are necessary to offer 90% power at 0.05 significant level according to 1:1 ratio of random grouping. Anticipating 10% of patients potentially non-assessable according to previous experience on 12-month study, 124 randomized patients in total are needed.

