#### Analysis

The final results will be presented on an intention-to-treat (ITT) basis. All data will be presented as percentages or mean ± standard deviation (SD). The comparison of data will be performed using the Chi-squared test (categorical variables) or Student’s t test (continuous variables). Cumulative incidences of end points in 12 months after PCI will be calculated using Kaplan-Meier methods. Log-rank tests will be used for comparisons between groups. Possible covariables will be incorporated in the analysis if certain important baseline levels are still not matched after randomization. Mean imputation will be used to handle missing data. A *p*-value < 0.05 will be considered significant. All statistical analyses will be performed using the Statistical Package for Social Sciences (SPSS), version 20.0 (SPSS Inc., Chicago, IL, USA). The results will be published by chief investigator and major contributors.

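### Single mean imputation, with the mean left unspecified, either understates the standard error or dilutes the estimated effect on LVMI

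*Protocol article*

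**What the plan says.** The primary end point is continuous. Under Primary end point, the protocol article states: "The primary end point in this study is the change between baseline and follow-up LVMI". Echocardiography is scheduled at baseline, 3 months and 12 months (Table 1).

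The Analysis section compares continuous variables with Student's t test and adds: "The final results will be presented on an intention-to-treat (ITT) basis". Its only rule for gaps is: "Mean imputation will be used to handle missing data". It does not say which mean is used, or whether the follow-up LVMI or the change is filled in. It gives no variance correction and no sensitivity analysis.

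The Sample size section expects some loss: "Anticipating 10% of patients potentially non-assessable according to previous experience on 12-month study". It therefore goes from 56 to 62 per arm, and "124 randomized patients in total are needed".

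The section on exclusion criteria during follow-up allows patients to be removed for poor compliance, loss to follow-up, or because staying in is harmful to them.

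**The concern.** A t test treats every value as an independent observation. A patient filled in with a mean adds to the count but brings no information. What this does depends on the mean chosen, which the protocol leaves open:

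- **Arm mean.** The filled values sit at the centre of their own arm. The standard deviation falls and n rises, so the standard error is too small.
- **Overall mean.** The filled values are the same in both arms, so the arms are drawn together and the treatment difference shrinks.

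The error rate or the size of the primary result is therefore at stake. A patient seen at 3 months but not at 12 is also given a group average, although that patient's own earlier LVMI is known. If removal is related to outcome, as the listed reasons allow, an average value can hide worsening.

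**Working it through.** **Inputs from the protocol article.** Response rates 70% and 40%, 90% power, significance level 0.05, 56 per arm, 10% non-assessable, 124 in total (Sample size); change in LVMI (Primary end point); Student's t test and ITT (Analysis).

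**Assumptions, not in the protocol.** Data missing completely at random; normally distributed values in SD units; an illustrative true effect of 0.60 SD; a correlation of 0.3 to 0.85 between baseline and follow-up LVMI. The type I error for imputed change does not depend on the effect size or the SD.

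**1. The plan's own figure.** Two-sided, pooled variance, no continuity correction:

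n = [1.96 × √(2 × 0.55 × 0.45) + 1.2816 × √(0.7 × 0.3 + 0.4 × 0.6)]² / 0.30² = (1.379 + 0.860)² / 0.09 = 55.7, so 56 per arm, with power 90.2%.

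56 × 1.1 = 61.6, so 62 per arm and 124 in total. Both figures reproduce. If 56 of 62 are observed, 6 per arm (9.7%) are missing.

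**2. Arm mean, change imputed.**

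- SE reported by the t test: √(55/61) × √(2/62) = 0.1705 SD.
- True SE, since only 56 per arm carry information: √(2/56) = 0.1890 SD.
- Ratio: 0.902, so the reported SE is about 10% too small.
- Type I error: the critical value 1.980 (122 df) acts as 1.980 × 0.902 = 1.786 on a t distribution with 110 df, which gives 7.7%. The large-sample form 2 × [1 − Φ(1.96 × 0.90)] gives 7.8%. Simulation runs gave 7.3% to 7.8%.

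**3. Arm mean, 12-month level imputed, change then computed.** The filled patients still differ through their own baselines, so the variance shrinks less. In simulation the reported SE is about 5% too small and type I error is 6.1% to 6.5% over the assumed correlations.

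**4. Overall mean.** The filled patients contribute no difference between arms, so the estimate is multiplied by 56/62 = 0.903, and 0.60 becomes 0.54 SD. The reported SE shrinks with it and matches the true one (0.170 against 0.171). Simulated type I error is 4.9%, and power is 88.2% against 88.1% for observed cases alone.

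**5. No imputation.** With 56 observed per arm, simulated type I error is 5.1%, the reported SE is correct (0.1885 against 0.1887) and the estimate is unbiased.

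| Reading of the rule, about 10% missing | Type I error | Estimate of a 0.60 SD effect |
|---|---|---|
| Arm mean of change | 7–8% | 0.60 |
| Arm mean of 12-month level | about 6% | 0.60 |
| Overall mean of change | about 5% | 0.54 |
| Observed data only | about 5% | 0.60 |

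**If more were missing.** The protocol gives no rate above 10%. At an assumed 20%, arm-mean imputation of the change gives 11.7% by the large-sample form, and the overall mean reduces 0.60 to 0.48.

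**The case against.** A reader might infer that the primary p-value is invalid whichever mean is used. The protocol does not support that. With the overall mean and data missing completely at random, the test keeps its 5% level and loses no power against observed cases; only the estimate and its interval suffer. Because the rule does not name the mean, validity of the p-value is not assured, rather than shown to be lost.

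Other points also stand:

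- The 7–8% figure belongs to the least favourable reading. What a patient lacks is a follow-up LVMI, and imputing that level gives about 6%.
- The protocol calls the 10% non-assessable and does not say in terms that these patients will be imputed. That they would be is an inference from the ITT statement read with the imputation rule.
- Missingness may be lower than planned: research nurses prompt attendance, and a visit after withdrawal is arranged where possible.
- No direction or size of outcome-related dropout is documented, and an analysis of observed cases alone would be exposed to it as well.
- The rule need not reach MACEs. The Analysis section uses Kaplan-Meier and log-rank methods for cumulative incidence of end points and does not say that events are imputed.

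What does not stand is the defence that an unseen analysis plan will settle the matter. The method is fixed in the text, and each way of completing it does some harm.

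**Conclusion.** The concern holds in a limited form. A weak method is prespecified for the primary end point and leaves open which of two harms follows. At the protocol's own 10%, the arm mean raises type I error from 5% to between about 6% and 8%, with a standard error about 5% to 10% too small. The overall mean leaves the error rate near 5% and understates the effect by about 10%. These sizes are moderate. They rest on 62 per arm, data missing completely at random, and the non-assessable patients being the ones imputed. Under any of these readings, information from the patient's own earlier visits is not used to inform the missing value, and outcome-related dropout is left unexamined.

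**What to change.** Delete mean imputation for the primary end point. Replace it with one of two methods:

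- a likelihood-based repeated-measures model for LVMI change at the planned 3- and 12-month visits, on all observed data, with arm, visit, arm-by-visit interaction, baseline LVMI and the stratification factors; or
- multiple imputation that uses baseline and 3-month LVMI.

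Either is acceptable. Add a sensitivity analysis in which missing outcomes are shifted in the unfavourable direction, and state the missingness assumption behind the main analysis. This correction does not require a change to the timing of the primary end point.

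The cost is a paragraph of text and slightly more programming, with no extra patients or visits. The sample size stands, since 56 evaluable patients per arm already give about 90% power on the protocol's own sizing. The change should be made before unblinding.

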## Discussion

The study is the first investigator-initiated, prospective study to evaluate the treatment effect of trimetazidine on ventricular remodeling in CAD patients undergoing PCI with LVH. The result of the study will confirm whether trimetazidine improves ventricular remodeling, angina and myocardial ischemia.

Cardiac hypertrophy is a common pathological change in cardiovascular diseases. In the early stage, it is an adaptive response of the heart to the overload. With the development of the disease, the myocardial structure will be disordered and the compliance will be decreased. The mechanism of CAD associated with LVH is a complex process involving multiple factors, such as blood pressure, catecholamine and renin-angiotensin-aldosterone system. It is characterized by hypertrophy of cardiomyocytes and changes in coronary microcirculation. Coronary microcirculation networks are the metabolic site of myocardium, and their lesions can cause the decline of coronary reserve function and the changes of myocardial ultrastructure, which are closely related to the maintenance of myocardial energy metabolism.

Myocardial energy metabolism disorders occur prior to typical morphological changes in ventricular hypertrophy [23]. During the development of cardiac hypertrophy, the energy metabolism of hypertrophic cardiomyocytes changes from aerobic oxidation to anaerobic fermentation. Metabolic therapy is to improve the process of energy metabolism so that cardiomyocytes can get more energy. Trimetazidine is a metabolic agent with a protective effect on cardiomyocytes. It mainly inhibits the oxidation of free fatty acids, activates pyruvate dehydrogenase, increases the oxidation of glucose and the production efficiency of cardiac adenosine triphosphate (ATP), as well as maintains myocardial contractile function [24]. It also directs free fatty acids to synthesize phospholipids, which involve in the construction of cell membrane. Accordingly, by improving the environment of the cell and promoting the construction of membrane, trimetazidine might protect the ultrastructure of myocardium and is likely to inhibit or even reverse the cardiac hypertrophy.

Previous study has showed trimetazidine minimizes myocardial reperfusion injury during PCI and improves global and regional wall motion at one and 3 months after PCI [20]. In this previous study, 52 acute coronary syndrome (ACS) patients were included and randomized into trimetazidine group and placebo group. Echocardiographic measurements before revascularization revealed 40% patients in trimetazidine group had an ejection fraction < 50% versus 33% patients in placebo group. The number of patients with an ejection fraction < 50% was significantly reduced in trimetazidine group compared with placebo group after PCI (11% vs. 16%, *p* = 0.046 at 1 month; and 4% vs. 16%, *p* = 0.017 at 3 months). A significant improvement in regional wall motion was noted after treatment with trimetazidine compared with placebo. Three months after PCI, inferior left ventricular wall hypokinesia had improved in 66.7% trimetazidine recipients and in 42.9% placebo recipients (*p* = 0.05), and anterior wall hypokinesia had improved in 72.7% in trimetazidine group and in 33.3% in placebo group (*p* = 0.04). However, the researchers only focused on the improvements for 3 months, long-term impact of trimetazidine on left ventricular remodeling in CAD patients undergoing PCI is still unclear. Subsequent Korean study suggested that trimetazidine treatment in non-ST segment elevation myocardial infarction (NSTEMI) patients provided improvements in left ventricular end diastolic volume [25]. The adjuvant treatment with trimetazidine after drug-eluting stent implantation was also confirmed to have a beneficial effect on left ventricular function and structure in elderly multivessel CAD patients with diabetes mellitus [26]. Nonetheless, these studies were not focused directly on patients with LVH. The study we proposed is intended to provide evidence for further clinical application of trimetazidine in CAD patients with LVH.

There were also studies in recent years exploring possible molecular mechanisms. The rat model of aortic constriction was established to induce myocardial metabolic disorder within 7 days, and it was found that trimetazidine pretreatment could improve the myocardial energy metabolism by reducing serum levels of oxidative stress markers, attenuating the induction of genes related to myocardial hypertrophy, inhibiting the up-regulation of serum neuropeptide Y (NPY) levels, and further increasing the expression of myocardial NPY receptors [27]. This not only demonstrated that trimetazidine pretreatment could reverse acute metabolic disorders, but also revealed the underlying pathophysiological process of metabolic remodeling before the onset of myocardial remodeling.

Other researchers verified in vivo and in vitro that trimetazidine could effectively inhibit myocardial fibrosis through nicotinamide adenine dinucleotide phosphate (NADPH) oxidase-reactive oxygen species (ROS)-connective tissue growth factor (CTGF) signaling pathway [28]. However, those results were obtained just from animals and need to be supported by clinical trials.

In our study, stratified randomization will be used to reduce the possibility of variable imbalance. Thus, no difference will exist in the use of ACEI, ARB and aldosterone antagonist between groups. Nonetheless, it is possible that some baseline levels are still not matched after randomization. In this case, we believe that it occurs “by chance” and is a small probability event. Those variables (*p* < 0.05) will be adjusted. But in addition to statistical considerations, we will also assess the relationship between the adjusted covariates and the end points, rather than unselectively adjust them.

This study has some limitations. First, though the proposed study is designed as a randomized, placebo-controlled study, it is a single-center study, which may cause the baseline drift of the selected patients. Second, the causes of LVH are various. Hypertension, obesity and other pathologic disorders can cause an increase in the hemodynamic burden and lead to LVH. Thus, the findings of this study may not be applied to LVH caused by all diseases.

In conclusion, this trial will first investigate trimetazidine treatment (35 mg twice a day for 12 months) on the ventricular remodeling in CAD patients with LVH. We expect that the study results will confirm whether trimetazidine treatment can significantly improve ventricular remodeling.

## Data Availability

Not applicable.

## Abbreviations

CAD: Coronary artery disease
PCI: Percutaneous coronary intervention
LVH: Left ventricular hypertrophy
MACEs: Major adverse cardiovascular events
LVM: Left ventricular mass
LVMI: Left ventricular mass index
ChiCTR: Chinese clinical trial registry
ACEI: Angiotensin-converting enzyme inhibitor
ARB: Angiotensin receptor blocker
6-MWT: 6-min walk test
CRFs: Case report forms
CBC: Complete blood count
ALT: Alanine aminotransferase
AST: Aspartate aminotransferase
Scr: Serum creatinine
BUN: Blood urea nitrogen
LDL-C: Low-density lipoprotein cholesterol
NT-proBNP: N-terminal pro-B–type natriuretic peptide
IVST: Interventricular septum thickness
LVEDd: Left ventricular end-diastolic dimension
LVPWT: Left ventricular posterior wall thickness
SF-36: Short form-36
ITT: Intention-to-treat
SD: Standard deviation
SPSS: Statistical Package for Social Sciences
ATP: Adenosine triphosphate
ACS: Acute coronary syndrome
NSTEMI: Non-ST segment elevation myocardial infarction
NPY: Neuropeptide Y
NADPH: Nicotinamide adenine dinucleotide phosphate
ROS: Reactive oxygen species
CTGF: Connective tissue growth factor
ECG: Electrocardiography
UA: Uric acid
TC: Total cholesterol
HDL-C: How-density lipoprotein cholesterol
TG: Triglyceride
cTnT/cTnI: Cardiac troponin-T/ cardiac troponin-I
ULN: Upper limit of normal range
eGFR: Estimated glomerular filtration rate
LVEF: Left ventricular ejection fraction
